### Study design

This is a prospective, randomized controlled trial to evaluate the efficacy of adjuvant radiotherapy for locally advanced EGJ adenocarcinoma after D2 resection. The trial was conducted at the Cancer Hospital of the University of Chinese Academy of Sciences (Zhejiang Cancer Hospital). We anticipated that adjuvant radiotherapy can improve the 3-year DFS by 10%, thus providing strong evidence for adjuvant therapy for locally advanced EGJ adenocarcinoma. Our study has been registered at http://clinicaltrials.gov (ID: NCT03973008).

After providing the signed informed consent, eligible subjects will be randomly assigned to receive adjuvant chemotherapy plus chemoradiotherapy (experimental group) or adjuvant chemotherapy alone (control group) in a ratio of 1:1. Randomization will be stratified by whether the EGJ is invaded or not and by postoperative stage. Patients in adjuvant chemotherapy group (control group) will receive eight cycles of SOX regimen chemotherapy; while patients in adjuvant chemotherapy plus chemoradiotherapy group (experimental group) received two cycles of SOX, then concurrent chemoradiotherapy (45 Gy of radiation with S-1 concurrent oral chemotherapy), followed by four additional cycles of SOX. All adjuvant therapy should begin within 4–6 weeks after surgery. Patients enrolled in this study should complete 3-year follow-up after randomization. The date and location of the first recurrence, as well as the date of death, will be documented. The study flow chart is shown in Fig. 1, and the schedule of enrollment, interventions, and assessments is shown in Fig. 2. The Standard Protocol Items: Recommendations for Interventional Trials (SPIRIT) checklist is provided in Additional file 1.

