### Outcome measures

#### Primary endpoint

The 3-year DFS is the primary endpoint of this study. It is defined as the percentage of patients without locoregional recurrence, distant metastasis, or tumor-related death at 3 years measured from the date of randomization. Once a patient is lost after the last follow-up, his/her survival time will be censored at the last date the patient is known to be alive.

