### Follow-up

Patients should be followed up once every 3 months within 2 years after operation and once every 6 months 2 years after operation until 5 years. Follow-up contents include physical examination, performance status monitoring, weight monitoring, routine blood test, blood chemistry, tumor markers (including CEA and CA19-9), adverse events, and QoL assessment. Chest, abdominal, and pelvic CT should be performed every 6 months, and gastroscopy is recommended once a year. If new symptoms or symptoms worsen, patients should receive follow-up visit at any time. The recurrence and/or metastasis must have biopsy or clinical imaging evidence, and the time and location of recurrence and/or metastasis should be recorded in detail.

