### Statistical analysis

In this study, the sample size was estimated by statisticians. The 3-year DFS of the experimental group is expected to be increased from 47 to 60% (δ=0.13), which provides strong evidence for adjuvant treatment of locally advanced EGJ adenocarcinoma. With a one-sided alpha =0.05 and 1 − *β*=0.8, 172 per group would be necessary, and 206 endpoint events need to be observed. Given an estimated dropout rate of 10%, the required total sample size would be 378. Patients enrolled in this study would be randomly divided into experimental group and control group, stratified by whether the EGJ is invaded or not and by postoperative stage. The ratio of the two groups was 1:1.

The analysis was based on the intention-to-treat (ITT) population. The ITT population should include all patients receiving randomization. Per-protocol (PP) population should include all patients who received at least two cycles of chemotherapy and completed radiotherapy for experimental group and received at least four cycles of chemotherapy for control group.

Comparison of baseline data between the two groups: if the quantitative data is normal distribution, *t* test is used; if it is not, rank sum test is used; *χ*^2^ test is used for qualitative data. Survival analysis is carried out by SPSS software package. Log rank *χ*^2^ analysis is used for comparison between the two groups, and Cox regression model is used in multivariate analysis. *χ*^2^ test is used to compare the recurrence rate, metastasis rate, and the incidence of side effects between the two groups. Two-tailed test is used, and *p* < 0.05 is considered statistically significant.

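### The 206-event target cannot be reached on the 3-year horizon used to define the primary endpoint and follow-up, and the power that results depends on which of two stated alphas applies

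*Protocol article*

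**What the plan says.** Five statements in the protocol article bear on this point.

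- **Primary endpoint:** "The 3-year DFS is the primary endpoint of this study". The section then defines it as a percentage without a DFS event at 3 years from randomization, and adds a censoring rule for patients lost to follow-up.
- **Study design:** "Patients enrolled in this study should complete 3-year follow-up after randomization".
- **Follow-up:** visits every 3 months for the first 2 years, then "once every 6 months 2 years after operation until 5 years", counted from the operation.
- **Statistical analysis, sample size:** 3-year DFS of 47% against 60%, "With a one-sided alpha =0.05", 80% power, "172 per group would be necessary, and 206 endpoint events need to be observed". Then: "Given an estimated dropout rate of 10%, the required total sample size would be 378".
- **Statistical analysis, methods:** log-rank comparison, Cox regression for multivariate analysis, ITT on all randomized patients, and "Two-tailed test is used" with significance at p < 0.05.

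Trial status gives recruitment from 1 July 2019 to 30 June 2022, which is 3 years of accrual.

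**The concern.** The endpoint definition and the Study design section describe a 3-year horizon per patient. The event count belongs to a time-to-event design in which patients are observed longer than that. The Follow-up section offers a third horizon, 5 years after operation. The article does not say whether a recurrence in year 4 counts towards the primary analysis.

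A team that follows the endpoint definition would analyse about 160 to 176 events and still describe the trial as sized on 206. A team that follows the sample-size sentence would wait for events that the endpoint definition leaves out. The trial is open label and has no external data monitoring committee, so the horizon of the primary analysis should not be left to a later choice between these readings.

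The two statements about sidedness add to the problem, because they decide how much power a 3-year cut would have.

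**Working it through.** **Inputs.** From Statistical analysis: 3-year DFS 0.47 and 0.60, 1:1 allocation, 172 per group, 206 events, 10% dropout, total 378. From Trial status: 3-year accrual. Assumed here: exponential DFS, proportional hazards and uniform accrual. Where loss is modelled, it is exponential and reaches 10% by year 3. The interval between operation and randomization is ignored.

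**1. Reproduce the event target.**
HR = ln 0.60 / ln 0.47 = 0.677, so |ln HR| = 0.3907.
Schoenfeld: D = 4(z_α + z_β)² / (ln HR)².
- Two-sided 0.05: 4 × (1.960 + 0.842)² / 0.1527 = 205.7, so 206. This matches the plan.
- One-sided 0.05: 4 × (1.645 + 0.842)² / 0.1527 = 162. This does not match.

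**2. Reproduce the sample size.**
The hazards are −ln 0.47 / 3 = 0.2517 and −ln 0.60 / 3 = 0.1703 per year. With 3-year accrual, analysis 3 years after the last entry and all follow-up counted (3 to 6 years per patient, no loss), the event probabilities are 0.670 and 0.530.
- n per arm = 206 / 1.200 = 171.6, so 172. This matches the plan.
- Formulas for comparing two percentages give 181 per arm (one-sided) or 230 (two-sided). Neither matches.

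**3. Events with a 3-year cut.**
- 344 patients, no loss: 172 × (0.53 + 0.40) = 160.
- 378 patients, no loss: 189 × 0.93 = 176.
- 378 patients, 10% loss by year 3: 189 × 0.888 = 168.
- Outer bound, both arms at the control rate and no loss: 378 × 0.53 = 200.

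All are below 206, and none depends on sidedness.

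**4. Log-rank power with a 3-year cut.**
Power = Φ(√D / 2 × 0.3907 − z_α). For D = 160 the first term is 2.471.

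| Events | Patients | Two-sided 0.05 | One-sided 0.05 |
|---|---|---|---|
| 160 | 344, no loss | 69.5% | 79.6% |
| 168 | 378, 10% loss | 71.6% | 81.2% |
| 176 | 378, no loss | 73.6% | 82.8% |

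A direct comparison of the two 3-year percentages with 172 per group has similar two-sided power: SE = √(0.4891 / 172) = 0.0533, and Φ(0.13 / 0.0533 − 1.96) = 68.4%.

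**5. Events under the existing 5-year schedule.**
Analysis is 3 years after the last entry, with each patient capped at 5 years.

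| Patients | Loss | Events | Two-sided power |
|---|---|---|---|
| 344 | none | 203 | 79.4% |
| 378 | 10% by year 3 | 209 | 80.6% |
| 378 | none | 223 | 83.0% |

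**6. Dropout allowance.**
344 × 1.1 = 378.4, but 378 × 0.9 = 340. To keep 344 after 10% loss takes 344 / 0.9 = 382.2, so 383. If dropouts contribute nothing, 340 patients give 170 × 1.200 = 204 events and 79.7% two-sided power.

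**The case against.** The best defence is that the 3 years in Study design are a minimum per patient. The Primary endpoint section has a censoring rule, the analysis uses log-rank and Cox, and visits run to 5 years. Read that way, Study design, Follow-up and Statistical analysis largely fit together, 172 and 206 reproduce exactly, and the fault is loose wording of the endpoint. This is probably what was intended. It does not remove the conflict, because the endpoint is still written as a percentage at 3 years, and on that definition 206 events cannot occur.

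Two stronger readings are tempting, and the document supports neither.

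- **That the trial simply has about 69% power instead of 80%.** That figure needs the two-tailed test, 344 patients and truncation at 3 years together. At the one-sided 0.05 to which the protocol attaches its 80%, 160 events give 79.6%, and 378 patients give 81–83%.
- **That 206 events require follow-up of up to six years.** Six years for the earliest patients is how 172 per group was evidently derived, but the planned 378 patients reach 209 to 223 events within the existing 5-year schedule.

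A data cut-off rule may also stand in the full protocol or the SAP, so its absence from an article is not the point here. The point is that stated figures disagree. The dropout slip is small, and since patients who drop out are censored and stay in the ITT set, the 340 figure is pessimistic.

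**Conclusion.** The point holds as a contradiction between the stated endpoint horizon and the stated event target. On a 3-year horizon the trial sees 160 events (344 patients) or 168 to 176 (378 patients), which is 30 to 46 short of 206. Two-sided power is then 69.5% to 73.6%, and one-sided power 79.6% to 82.8%. How far power falls short therefore turns on the one-sided/two-tailed conflict within the Statistical analysis section, and the two issues need to be settled together. Two-sided 0.05 is the reading that agrees with both the event target and the analysis rule.

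The shortfall in events without loss follows directly from the protocol's own 3-year rates. The match at 172 per group, the loss-adjusted counts and the 5-year counts rest on exponential DFS, uniform accrual and, where stated, the assumed loss pattern; the log-rank power figures rest on proportional hazards. The dropout arithmetic is a minor correction.

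**What to change.** 1. In Primary endpoint, define the primary endpoint as DFS time from randomization, compared by log-rank using all follow-up. Keep 3-year Kaplan-Meier DFS per arm as the descriptive summary.
2. In Statistical analysis, tie the primary analysis to 206 DFS events, expected by about 3 years after the last randomization.
3. In the sample-size sentence, replace the one-sided alpha with two-sided 0.05, so that it agrees with the 206 events and the two-tailed rule.
4. In Study design, say that 3 years is the minimum follow-up and that DFS events continue to be collected under the 5-year schedule until the analysis cut-off. Align Follow-up with this.
5. Restate the dropout figure: 378 less 10% leaves about 340, not 344.

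The cost is a wording amendment. No added visits and no added patients are needed.

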#### Principles of interruption or discontinuation of radiotherapy

When the acute grade 3 radiation toxicities occurs, radiotherapy should not be interrupted and symptomatic treatment should be given. If it does not recover to grade 0–1 within 7 days, radiotherapy should be interrupted and restarted after the grade of toxicity return to 0–1. If the same toxicities of above grade 2 reoccur, radiotherapy should be terminated. When radiotherapy is terminated, S-1 should be terminated at the same time.If any grade 4 adverse reactions except leukopenia occurred, radiotherapy should be discontinued. When the adverse reactions recover to grade 0–1, restart radiotherapy, but not chemotherapy.Dose of radiation should not be adjusted unless new adverse reactions occur or the original adverse reactions are aggravated.

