### Ethics

This study was carried out according to the Declaration of Helsinki. The protocol, the informed consent form, and the case report form have been reviewed and approved by the medical ethics committee of our hospital (IRB-2019-196), and the main members who participated in the study have obtained the certificate of the Good Clinical Practice (GCP) course.

Participation in this study is completely voluntary. All patients will be informed of the study process, benefits, costs, potential adverse reactions, and other alternative treatment options in detail before entering this study, and then sign the informed consent. All the signed informed consent will be kept by the principal investigator. After entering this study, patients could withdraw from the study at any time for any reason and receive other alternative treatment.

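### As worded, the per-protocol set keeps control patients irradiated before recurrence and drops experimental patients whose radiotherapy was stopped under the protocol's own rules, so its contrast can be biased in a direction the article does not fix (minor)

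*Protocol article*

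**What the plan says.** The Statistical analysis section of the protocol article states "The analysis was based on the intention-to-treat (ITT) population", with every randomized patient included. It then defines the PP set inclusively, admitting everyone who meets one condition per arm: "received at least two cycles of chemotherapy and completed radiotherapy for experimental group and received at least four cycles of chemotherapy for control group".

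Under Study design, control patients "will receive eight cycles of SOX regimen chemotherapy", and experimental patients "received two cycles of SOX, then concurrent chemoradiotherapy (45 Gy of radiation with S-1 concurrent oral chemotherapy), followed by four additional cycles of SOX".

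Three other sections bear on who ends up in the set:

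- Principles of interruption or discontinuation of radiotherapy: radiotherapy is terminated when certain toxicities recur. After grade 4 reactions other than leukopenia have resolved, the instruction is to "restart radiotherapy, but not chemotherapy".
- Exit criteria: these include being untreatable according to the study scheme, and withdrawal at the patient's request.
- Ethics: "patients could withdraw from the study at any time for any reason and receive other alternative treatment".

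No sentence ties meeting an exit criterion to membership of the PP set. No PP hypothesis, test or decision rule is given.

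**The concern.** A PP set is normally reported to show the effect of the treatments as delivered. Here the component under test is radiotherapy, and the definition handles it in only one arm. Completion is required in the experimental arm, while its absence is not required in the control arm. The trial is open label and withdrawn patients may take other treatment, so adjuvant radiotherapy in a control patient is possible.

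Membership is also decided after randomization, while DFS runs from randomization (Primary endpoint). Patients who stop radiotherapy because of toxicity, frailty or early relapse leave the experimental arm's PP set. Some of them will have been managed exactly as the protocol directs. If these patients have a worse prognosis, removing them raises experimental DFS whether or not radiotherapy works.

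What is at stake is how a PP result would be read beside the ITT result, above all if ITT were inconclusive. The article gives the PP set no supportive label.

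**Working it through.** The article gives no figure for the PP set, so there is none to reproduce. The check is of the wording, then of the possible size of each mechanism.

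**1. The criteria applied to four patients** (reading cycles of chemotherapy as SOX cycles)

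| Patient | PP as worded? |
|---|---|
| Control, 4 SOX cycles, then adjuvant radiotherapy before recurrence | Yes |
| Control, chemotherapy stopped after cycle 3 for grade 4 toxicity, as Dose modification directs | No |
| Experimental, 2 SOX cycles, grade 4 toxicity during chemoradiotherapy, radiotherapy restarted and completed, no further chemotherapy | Yes |
| Experimental, 2 SOX cycles, radiotherapy terminated for recurrent toxicity as the protocol directs | No |

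The last three were all managed under the protocol's rules, yet their PP status differs.

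**2. How unequal the criteria are.** Inputs: 3-week cycles (Chemotherapy regime) and 5 weeks of radiotherapy (Concurrent chemoradiotherapy regime), assuming no gaps or delays.

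- By SOX cycles: 2/6 = 33% versus 4/8 = 50%.
- By planned treatment time: experimental (2×3 + 5) / (2×3 + 5 + 4×3) = 11/23 weeks = 48%; control (4×3) / (8×3) = 12/24 weeks = 50%.

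**3. Time needed to qualify.** With no true effect and exponential DFS of 47% at 3 years in both arms, λ = −ln(0.47)/3 = 0.252 per year. DFS among those event-free at week w is 0.47·exp(λ·w/52.18).

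- Week 9: 49.1%. Week 11: 49.6%. Week 12: 49.8%.
- End of radiotherapy (week 11) against start of control cycle 4 (week 9): +0.5 points.
- End of radiotherapy (week 11) against end of control cycle 4 (week 12): −0.2 points.

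**4. Selection on completed radiotherapy, no true effect.** If a fraction f of an arm misses its criterion and has 3-year DFS q, the PP DFS of that arm is (47 − f·q)/(1 − f). The article gives neither f nor q; the values here are assumptions.

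- q = 30%. Experimental f = 15 to 25%: (47 − 4.5)/0.85 = 50.0% to (47 − 7.5)/0.75 = 52.7%. Control f = 5 to 10%: (47 − 1.5)/0.95 = 47.9% to (47 − 3)/0.90 = 48.9%. Spurious gain: 50.0 − 48.9 = 1.1 to 52.7 − 47.9 = 4.8 points.
- q = 40%, same f. Experimental 48.2 to 49.3%, control 47.4 to 47.8%. Spurious gain: about 0.5 to 2 points.
- Equal f and q in both arms: zero.

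**5. Irradiated controls, planned effect true.** If a fraction c of control PP patients gets the full radiotherapy effect, control DFS is 47 + 13c and the difference is 13(1 − c). The values of c are assumptions.

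- c = 5%: 12.35, about 12.4 points.
- c = 10%: 11.7 points.
- c = 20%: 10.4 points.

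The mechanism in step 4 can push the contrast up; the one in step 5 pushes it towards the null.

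**The case against.** The strongest reply is that nothing is decided on this set. The trial tests superiority, ITT is the stated basis, and the article condenses a fuller protocol, so detailed PP exclusions may sit in an analysis plan that is not shown. The first two points stand and keep the severity low. The third stands only in part, because the article states a positive rule of inclusion, and that rule as written admits irradiated controls.

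Regimens with different components also need different criteria. This stands too. A reader might infer from 33% versus 50% of SOX cycles that the experimental criterion is lax, but that count leaves out five weeks of radiotherapy with S-1. By treatment time the criteria nearly match.

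A reader might further infer that the PP set is selected in favour of the experimental arm. The document does not support that as fact. Only the completed-radiotherapy condition plausibly works that way, and its size comes entirely from assumed rates. The low SOX minimum keeps under-treated experimental patients in, the control criterion also removes patients who do poorly, and the difference in qualifying time is too small and uncertain in sign to matter.

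Nor is crossover documented. Alternative treatment is mentioned only for patients who withdraw, Ancillary and post-trial care restricts ancillary care to treatment-related complications, and no crossover rate is given. It remains a possibility that the definition does not handle, and it would work against the experimental arm.

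**Conclusion.** The point holds in limited form. The PP criteria are arm-specific and post-randomization. As worded they retain control patients irradiated before recurrence and exclude experimental patients whose radiotherapy was terminated under the protocol. The PP contrast can therefore be biased, by selection that plausibly favours the experimental arm and by dilution towards the null.

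The net direction and size cannot be determined from the article. The illustrative ranges (about 0.5 to 5 points of spurious gain, and about 0.6 to 2.6 points of dilution, 13 − 12.35 to 13 − 10.4) depend on assumed completion rates, crossover rates and prognosis. The ITT conclusion is untouched. Severity is minor.

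**What to change.** Amend the population definition in the Statistical analysis section:

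1. Exclude from the PP set any patient, in either arm, who received non-assigned antineoplastic treatment before recurrence, naming radiotherapy in the control arm.
2. If the minimum-exposure criteria are kept, start PP DFS at one common landmark, about week 12 of treatment, when both criteria can be met on schedule. Say how patients who reach their criterion later are handled.
3. Label the PP analysis as supportive to ITT.

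The landmark removes the difference in qualifying time. It does not remove selection on tolerating radiotherapy, which is why the label is needed.

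The cost is small: a change of wording and a slightly smaller PP set. Under the exponential 47% assumption about 5.6% of control patients would have an event before week 12, and most of these would miss the four-cycle criterion anyway. The exclusion needs the type and date of any non-assigned treatment to be recorded.

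A broader redefinition, such as all patients who started the assigned regimen, is not recommended here. It would keep stops for toxicity, but it would also count as per protocol experimental patients who were never irradiated.

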### Study population

#### Inclusion criteria

Voluntary participation and written informed consent.Aged older than 18 years and younger than 70 years, gender unlimited.Confirmed that the tumor center was located between 1 cm above and 5 cm below the EGJ, regardless of invasion to the EGJ, and histopathological diagnosis of adenocarcinoma.Received transabdominal D2 radical operation, and R0 resection was performedAscites cytology was negative.Postoperatively classified as pathological stages IIB~IIIC.Eastern Cooperative Oncology Group (ECOG) performance status score 0–1.Laboratory tests: hemoglobin (Hb) > 9 g/dL; white blood cell (WBC) > 3 × 10^9^/L; absolute neutrophil count (ANC) > 1.5 × 10^9^/L; platelet (Pt) > 100 × 10^9^/L; bilirubin < 1.5 times the upper limit of normal value; alanine-glutamic transaminase (ALT) and alanine transaminase (AST) < 2.5 times the upper limit of normal value; and serum creatinine < 1.5 times the upper limit of normal value.Daily energy intake > 1500 kcal.

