### Randomization, sequence generation, and implementation

All potential participants will be initially screened by the designated pathologists and then further screened according to the inclusion criteria and exclusion criteria by the designated clinicians. Those eligible subjects who signed the consent will be randomized to either experimental group (adjuvant chemotherapy plus chemoradiotherapy) or control group (adjuvant chemotherapy alone) in a ratio of 1:1. Randomization will be stratified by whether the EGJ is invaded or not and by postoperative stage.

We adopt a mobile application software, developed by Fudan University Biostatistics Central Office (Shanghai, China), to perform randomization, using varied permuted block design with a block size 2–6. The generation of random allocation sequence is operated by Fudan University Biostatistics Central Office, and the principal investigator will be informed by text message to ensure allocation concealment. Then, the principal investigator will forward the message of treatment assignments to the designated investigators, who guarantee the participants will be assigned to the corresponding intervention/control group.

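### The log-rank comparison named in the protocol does not carry the randomization strata; stratifying it would be a free gain in efficiency if EGJ invasion or stage is prognostic

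*Protocol article*

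**What the plan says.** The stratified allocation is stated in Study design, in Statistical analysis and in the randomization section, where it reads "Randomization will be stratified by whether the EGJ is invaded or not and by postoperative stage". Allocation is 1:1, "using varied permuted block design with a block size 2–6". The Inclusion criteria admit a span of stages: "Postoperatively classified as pathological stages IIB~IIIC". The categories of stage used as strata are not given.

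For the endpoint, "The 3-year DFS is the primary endpoint of this study". For the survival comparison, Statistical analysis names a log-rank chi-square: "analysis is used for comparison between the two groups, and Cox regression model is used in multivariate analysis". No strata are attached to the log-rank test, no covariates are listed for the Cox model, and neither analysis is labelled primary.

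On sample size the same section says "172 per group would be necessary, and 206 endpoint events need to be observed", for 3-year DFS rising from 47% to 60% with 80% power. It adds 10% for dropout to reach 378.

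**The concern.** Blocked randomization within strata makes the arms nearly equal on EGJ invasion and stage. The between-arm difference therefore varies less from one hypothetical trial to the next than it would under simple randomization. An unstratified log-rank variance does not take credit for this. If the factors predict DFS, the variance is too large for the design, the Z statistic has a standard deviation below 1 under the null, and the test rejects less often than its nominal level. Pooling strata with different hazards also moves the estimated hazard ratio towards 1 relative to the within-stratum value.

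What is at stake is efficiency: the same patients and events could give a more powerful test. The validity of a positive result is not at stake.

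**Working it through.** **1. The plan's own figures.** With exponential DFS, HR = ln(0.60)/ln(0.47) = 0.677, so (ln HR)² = 0.1527. Schoenfeld's formula for 1:1 allocation is D = 4(z_α + z_β)²/(ln HR)².

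- Two-sided 0.05, 80% power: 4(1.960 + 0.842)²/0.1527 ≈ 206 events, the stated figure.
- One-sided 0.05: 4(1.645 + 0.842)²/0.1527 ≈ 162 events.

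Recruitment is planned from 1 July 2019 to 30 June 2022 (Trial status), and Study design asks for 3 years of follow-up. With uniform accrual over 3 years and 3 further years, the mean event probability is 0.600. Then 206/0.600 = 343.3, or 172 per group, and 344 × 1.10 = 378.4, the stated 378. The sample size is thus that of an ordinary unstratified two-sided log-rank design. (That "With a one-sided alpha =0.05" stands beside "Two-tailed test is used" is a separate matter.)

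**2. Simulation set-up.** 344 patients; permuted blocks of 2, 4 and 6 within strata; 3 + 3 years; unstratified and stratified log-rank tests at two-sided 0.05; 5,000 trials per row. Control 3-year DFS is fixed at 47% overall.

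Assumed, because the documents do not give them: eight strata (IIB, IIIA, IIIB, IIIC by EGJ invaded or not), equal stage shares, EGJ invasion 50:50 with HR 1.2 (1.0 in the no-effect row), and a constant HR per stage step. Monte Carlo standard error is about 0.3 points for type I error and 0.6 points for power.

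For orientation, control 3-year DFS of 65/53/42/28% across the four stages averages 47%. It corresponds to [ln(0.28)/ln(0.65)]^(1/3) = 2.955^(1/3) ≈ 1.4 per step.

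**3. Type I error.**

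| HR per stage step | Unstratified | Stratified |
|---|---|---|
| 1.0 | 5.3% | 5.1% |
| 1.3 | 4.4% | 4.9% |
| 1.5 | 3.4% | 4.9% |
| 1.8 | 2.8% | 4.6% |
| 2.0 | 1.8% | 5.1% |

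The mechanism can be checked directly. The simulated standard deviation of the unstratified Z at 1.5 per step was 0.932, and 2[1 − Φ(1.96/0.932)] = 3.5%, against 3.4% simulated.

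**4. Power.** It depends on what the planned effect is taken to mean, so both readings are shown (unstratified / stratified).

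| HR per stage step | 47% vs 60% held overall | HR 0.677 held within strata |
|---|---|---|
| 1.0 | 80.4 / 79.4% | 80.0 / 79.1% |
| 1.3 | 79.5 / 81.3% | 77.8 / 78.9% |
| 1.5 | 78.6 / 83.8% | 74.8 / 79.4% |
| 1.8 | 78.6 / 87.1% | 67.6 / 77.9% |
| 2.0 | 78.1 / 89.4% | 62.7 / 78.7% |

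Power forgone by not stratifying: 1.1–1.8 points at 1.3, 4.6–5.2 at 1.5, 8.5–10.3 at 1.8 and 11.3–16.0 at 2.0. With no stage effect, stratifying costs about one point.

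**5. Why the two columns differ.** A fixed within-stratum HR of 0.677 gives a smaller overall difference than the one planned. With the 65/53/42/28% rates, raising each to the power 0.677 gives 74.7, 65.1, 55.6 and 42.3%, whose mean is 59.4%, not 60%. Part of the fall in the right-hand column is therefore a smaller overall effect, not the choice of test.

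**The case against.** The strongest reply is that an unstratified test is inferred from silence. The word is not printed, the Cox covariates are not listed and could include stage, and a condensed article may leave such details to an analysis plan that is not shown. This stands as a limit on certainty. It does not remove the point, because the article does name a test, in the section that also states the strata, and that test is described simply as a comparison of two groups.

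A reader might infer that the trial is underpowered, with power of about 68–75% at 1.5–1.8 per step. The documents do not support this. Those figures come from fixing 0.677 within strata, whereas the plan states its effect as 47% versus 60% for the groups as a whole. On that basis the unstratified test stays at about 78–80%.

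A reader might also take it as given that stage is strongly prognostic here. No DFS by stage or by EGJ invasion appears in the documents. Enrolling IIB to IIIC and choosing stage as a stratification factor make an effect plausible, but its size is unknown, and at 1.3 per step little is lost.

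Two further objections hold. The unstratified hazard ratio is a marginal effect and the stratified one a conditional effect, so their difference is not in itself bias. And eight strata is a guess: fewer stage categories would change the figures.

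**Conclusion.** The point holds as an efficiency improvement. The named log-rank test does not carry the factors that the randomization balances. If those factors are prognostic, the test is conservative and forgoes about 1–2, 5 or 8–10 points of power relative to a stratified test at assumed hazard ratios of 1.3, 1.5 or 1.8 per stage step. With 47% versus 60% holding overall, the planned power is essentially kept, and what is given up is a gain to about 84–87% at 1.5–1.8 per step. There is no false-positive inflation. The direction follows from the design; the size rests on the assumed stage effect, stage shares and eight strata.

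**What to change.** State that the primary DFS comparison is a log-rank test stratified by EGJ invasion and postoperative stage, using the same stage categories as the randomization, and write those categories down. Report the hazard ratio with its 95% CI from a Cox model stratified by the same factors. Keep the unstratified log-rank test as a sensitivity analysis.

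The cost is a change of wording. Both factors are recorded at randomization, and even with eight strata 344/8 = 43 patients per stratum on average is workable. Since the trial is open label and neither analysis is labelled primary, the choice should be fixed before any outcome data are compared by arm.
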